**7.1.8.4.7 Thromboembolic events related to the trial device.**

**7.1.8.5 Device defects.**

**7.1.8.6 Other adverse events.**

## **7.2 Trial Procedures**

### **7.2.1 Screening (within 30 days preoperatively)**

**7.2.1.1** Patients must sign the informed consent form before screening.

**7.2.1.2** Collect demographic data (gender, date of birth, weight, and height).

**7.2.1.3** NYHA functional class, vital signs (blood pressure, pulse).

**7.2.1.4** Laboratory tests: Complete blood count, blood biochemistry, coagulation function, and pregnancy test if necessary.

**7.2.1.5** Electrocardiogram (ECG), echocardiography (TTE or TEE).

**7.2.1.6** Record antiplatelet or anticoagulant medications.

**7.2.1.7** Randomization using a central randomization system.

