#### **Randomization Design**

The trial is designed as a randomized controlled trial (RCT), which is the gold standard for minimizing bias in clinical research. After a participant (or their legal guardian) signs the informed consent form and meets the eligibility criteria, they will be randomly assigned to either the test group or the control group using a centralized randomization system. This approach ensures that the two groups are balanced and comparable, reducing the risk of bias and improving the reliability of the results.

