#### **7.1.4 Investigational and Control Devices**

During surgery, the measurement of the tricuspid complex septal base length serves as a criterion for selecting the appropriate annulus size. Based on the results of randomization, the tricuspid Annuloplasty Ring from the appropriate test or control group is then selected.

Investigational Device: Annuloplasty Ring (Beijing Permed Biomedical Engineering Co., Ltd.) / (sizes 26、28、30、32、34、36).

Control Device: Edwards MC3 Ring (Edwards Lifesciences (Shanghai) Medical Products Co., Ltd.) / (sizes T26–36).

The control device is the device that has been approved for marketing by the National Medical Products Administration, and the usage method can be found in the product instruction manual.

Instructions for use of Annuloplasty Ring used in the trial:

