### **7.2.2 Surgical Treatment (Day 0, Surgery Day)**

**7.2.2.1** Monitor vital signs (blood pressure, pulse).

**7.2.2.2** Perform surgery using the designated device according to randomization results, recording anesthesia method, device model, and device performance evaluation.

**7.2.2.3** Transesophageal echocardiography (TEE) or transthoracic echocardiography (TTE) evaluation as needed.

**7.2.2.4** Record intraoperative complications and adverse events.

**7.2.2.5** Record intraoperative antiplatelet or anticoagulant medications.

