## **7.2.8 Trial Study Flowchart**

|                   |                                 |                                  |
|-------------------|---------------------------------|----------------------------------|
| Experimental flow | Screening period (Preoperative) | Follow-up period (postoperative) |
|-------------------|---------------------------------|----------------------------------|

| Visit Number                                                  |                           | V1     | V2                             | V3                         | V4         | V5      | V6           | V7        | V8      | V9         | V10        |
|---------------------------------------------------------------|---------------------------|--------|--------------------------------|----------------------------|------------|---------|--------------|-----------|---------|------------|------------|
| Days                                                          |                           | -30d~0 | Device
implant
a
tion | Discharg
e or
30d±7d | 3M±15
d | 6 M±30d | P12M±30
d | 2Y±3
d | 3Y ±30d | 4Y±3
0d | 5Y±3
0d |
| Informed Consent                                              |                           | X      |                                |                            |            |         |              |           |         |            |            |
| Inclusion/Exclusion
Criteria                               |                           | X      |                                |                            |            |         |              |           |         |            |            |
| Medical
history                                            |                           | X      |                                |                            |            |         |              |           |         |            |            |
| Vital Signs (BP, P)                                           |                           | X      | X                              | X                          |            |         |              |           |         |            |            |
| NYHA Functional
Class                                      |                           | X      |                                | X                          | X          | X       | X            |           |         |            |            |

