## Notes:

1. Laboratory test results and electrocardiogram (ECG) examinations conducted within 15 days prior to signing the informed consent form are valid as baseline assessments.
2. Ultrasound examination (either Transthoracic Echocardiography [TTE] or Transesophageal Echocardiography [TEE], choose one) as a baseline assessment should be performed by an ultrasound physician at our hospital before the surgery. Intraoperative Transesophageal Echocardiography (TEE) is recommended.

3. Laboratory tests include complete blood count (white blood cells, red blood cells, hemoglobin, platelets), blood biochemistry (creatinine, alanine aminotransferase, aspartate aminotransferase, total serum bilirubin), and coagulation function (activated partial thromboplastin time, prothrombin time, thrombin time).
4. Visit 3---Before discharge or 30±7 days post-operation, whichever comes first.
5. Pregnancy test: If the subject is a woman of childbearing age, a blood or urine pregnancy test should be performed as needed.
6. Record the use of antiplatelet or anticoagulant medications.
7. Cardiac ultrasound examinations should be performed by a qualified physician at our hospital; the same subject's ultrasound examinations should be conducted at the same center; follow-up results will be independently interpreted by a senior ultrasound physician.
8. The surgery should be performed by a designated surgeon.

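### Allocation is made at screening, up to 30 days before the ring is chosen, and anyone who leaves in between is in no analysis set

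*Protocol*

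**What the plan says.** Randomization is item 7.2.1.7, the last step of screening: "Randomization using a central randomization system". The flowchart in section 7.2.8 gives that visit (V1) a window of day -30 to day 0. Section 7.1.3 triggers allocation by consent and eligibility, not by surgery: a participant "signs the informed consent form and meets the eligibility criteria, they will be randomly assigned to either the test group or the control group".

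The flowchart row "Inclusion/Exclusion Criteria" is marked at V1 and not at V2, the implantation visit. The surgery-day list in section 7.2.2 covers vital signs, the operation, echocardiography as needed, and the recording of complications and medication. It starts from an allocation already made: "Perform surgery using the designated device according to randomization results". It contains no eligibility step.

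The arm is first used during the operation, after sizing (section 7.1.4): "Based on the results of randomization, the tricuspid Annuloplasty Ring from the appropriate test or control group is then selected".

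The three measures against bias in section 7.1.3 are randomization, training and monitoring. Neither blinding nor withholding of the allocation is mentioned. Section 7.1.5.3.4 lets participants withdraw at any time and lets investigators withdraw them for several reasons. Section 8.9 restricts the FAS to randomized patients who were implanted, makes the PPS a subset of the FAS, and also requires implantation for the SS.

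Note 1 to the flowchart adds: "Laboratory test results and electrocardiogram (ECG) examinations conducted within 15 days prior to signing the informed consent form are valid as baseline assessments".

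**The concern.** Between allocation and implantation an operation can be cancelled, the operative plan can change, consent can be withdrawn, or the patient can become ineligible. Several of the section 7.1.5.2 exclusions can arise within a month, for example fever or infection, stroke, worsening heart failure or pregnancy. If the arm is known when such a decision is made, the loss may depend on the arm. Because all three analysis sets require implantation, the loss then leaves no trace in the primary comparison, and the balance that randomization gave is not guaranteed among the patients analysed. The trial has 82 patients per arm and a 10-point margin, so a few patients matter when the result is close.

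Early allocation serves no analytical purpose, since the arm is not used until a ring is picked up in theatre.

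**Working it through.** **Plan's own sample size.** Inputs from section 8.2.1: success 95% in both arms, margin 10 points, one-sided alpha 0.025, power 80%.

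n per arm = (1.960 + 0.842)² × 2 × 0.95 × 0.05 / 0.10² = 74.6, so 75. The stated 75 is reproduced, and moving the time of randomization does not change it.

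**Length of the interval.** From V1, day -30 to day 0, to surgery: at most 30 days. Note 1 adds up to 15 days before consent for laboratory tests and ECG: 30 + 15 = 45 days at most. The screening heading allows 30.

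**Who is analysed.** Randomized but not implanted: excluded from the FAS, hence from the PPS, and excluded from the SS.

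**Effect of selective loss.** The primary rule compares the lower limit of the two-sided 95% Newcombe interval with -10%. With Wilson limits (l, u) for each arm,

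lower limit = (p1 - p2) - √[(p1 - l1)² + (u2 - p2)²].

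For 76/82 against 78/82: p1 = 0.9268, l1 = 0.8494, p2 = 0.9512, u2 = 0.9809. Lower limit = -0.0244 - √(0.0774² + 0.0297²) = -0.107.

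| Test | Control | What was lost before implantation | Lower limit | Result |
|---|---|---|---|---|
| 76/82 | 78/82 | nobody | -10.7% | fails |
| 76/81 | 78/82 | one test failure | -9.3% | passes |
| 75/82 | 78/82 | nobody | -12.2% | fails |
| 75/80 | 78/82 | two test failures | -9.5% | passes |
| 75/81 | 78/82 | one test success (from 76/82) | -10.9% | fails |
| 76/81 | 78/81 | one failure in each arm (from 76/82 and 78/82) | -10.3% | fails |

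The conclusion reverses only in the rows where every leaver is a test-arm failure.

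**Error rate in that same worst case.** Take true success rates of 85% (test) and 95% (control), exactly at the margin, with 82 randomized per arm. Exact binomial enumeration of the Newcombe rule, removing 0, 1, 2 or 4 would-be test failures, gives a false non-inferiority rate of 2.4%, 4.6%, 7.5% or 19.1%.

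**Effect of non-selective loss.** Power by the same normal approximation, Φ(0.10 / √(2 × 0.95 × 0.05 / n) - 1.960), is 80.2% at 75 per arm, 77.5% at 70 and 75.0% at 66. This costs power and does not bias the comparison.

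**The case against.** The strongest reply has five parts.

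- **The 30 and 45 days are upper bounds.** The window reaches day 0, so a site may randomize the day before surgery. Reaching 45 days needs consent on day -30 and tests at the limit of Note 1. That note covers laboratory tests and ECG, not the echocardiogram behind the regurgitation grade and the endpoint. This stands.
- **Safeguards exist.** A reader might infer that a newly ineligible patient would be implanted because nothing prevents it. The document does not support that: section 7.1.5.3.4 lets the investigator discontinue a participant for pregnancy, adverse events, disease progression or risk to health, and echocardiography is available on the day. What is missing is a documented re-check, not every means of stopping.
- **Knowledge of the arm is inferred.** A reader might take it that surgeon and patient both know the device for a month. The protocol never calls itself open-label and nowhere says that patients are told. It does not withhold the allocation from the surgical team either, and the surgeon must handle an identifiable ring. The inference is reasonable for the team and unproven for the patient.
- **The reversals are a worst case.** A reader might infer that any one or two losses overturn the result. They do not: losing a test success, or one failure in each arm, leaves the result unchanged. Identifying six-month failures before surgery would also be hard. This stands, and the reversals show sensitivity, not a forecast.
- **The root is the FAS definition, and early allocation helps supply.** Keeping all randomized patients in the main set would make the losses visible. It would still leave unimplanted patients with no six-month endpoint and no post-implantation value for the LOCF rule in section 8.7 to carry forward. Late allocation avoids most of these cases. The supply cost is real but limited, because rings are already sized during the operation.

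**Conclusion.** The point holds as a cheap improvement to the design. Followed exactly, the protocol permits allocation up to 30 days before the arm is needed, does not conceal it from the surgical team, and drops every patient lost in between from all analysis sets. The bias is possible, not shown. Its size depends on how many leave and how selectively, and the protocol states neither. In the worst case, one or two test-arm failures reverse a borderline result; if losses are unrelated to arm and prognosis, only power suffers. The conclusion assumes that the absence of any blinding text means the surgical team can see the allocation. Note 1 and the screening heading do not agree on how old baseline tests may be at surgery; this is a smaller, separate inconsistency.

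**What to change.** - Move item 7.2.1.7 from section 7.2.1 to section 7.2.2, with the same change in the synopsis. The central system then gives the allocation on the day of surgery, as late as practical before either ring is opened.
- Require a documented re-check of the section 7.1.5 criteria before that request, and mark Inclusion/Exclusion at V2 in the flowchart.
- Report by arm, with reasons, every patient randomized but not implanted.
- Reconcile Note 1 with the 30-day screening heading, so that one rule states how old baseline laboratory tests and ECG may be at surgery.

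The cost is a wording and flowchart amendment. The central randomization system is already in place and the sample size is unchanged. The practical downside is that both rings, in the sizes that may be needed, must be available for each case.

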### **7.2.2 Surgical Treatment (Day 0, Surgery Day)**

**7.2.2.1** Monitor vital signs (blood pressure, pulse).

**7.2.2.2** Perform surgery using the designated device according to randomization results, recording anesthesia method, device model, and device performance evaluation.

**7.2.2.3** Transesophageal echocardiography (TEE) or transthoracic echocardiography (TTE) evaluation as needed.

**7.2.2.4** Record intraoperative complications and adverse events.

**7.2.2.5** Record intraoperative antiplatelet or anticoagulant medications.

### **7.2.3 Clinical Evaluation at Discharge or 30 Days ( $\pm 7$ Days) Postoperatively (Whichever Comes First)**

**7.2.3.1** Monitor vital signs (blood pressure, pulse).

**7.2.3.2** NYHA functional class.

**7.2.3.3** ECG, echocardiography (TTE).

**7.2.3.4** Laboratory tests: Complete blood count, blood biochemistry.

**7.2.3.5** Record adverse events.

**7.2.3.6** Record antiplatelet or anticoagulant medications.

## **7.2.4 Clinical Evaluation at 3 Months ( $\pm 15$ Days) Postoperatively**

**7.2.4.1** NYHA functional class.

**7.2.4.2** ECG, echocardiography (TTE).

**7.2.4.3** Record adverse events.

**7.2.4.4** Record antiplatelet or anticoagulant medications.

## **7.2.5 Clinical Evaluation at 6 Months ( $\pm 30$ Days) Postoperatively**

**7.2.5.1** NYHA functional class.

**7.2.5.2** ECG, echocardiography (TTE).

**7.2.5.3** Record adverse events.

**7.2.5.4** Record antiplatelet or anticoagulant medications.

## **7.2.6 Clinical Evaluation at 12 Months ( $\pm 30$ Days) Postoperatively**

**7.2.6.1** NYHA functional class.

**7.2.6.2** ECG, echocardiography (TTE).

**7.2.6.3** Record adverse events.

**7.2.6.4** Record antiplatelet or anticoagulant medications.

## **7.2.7 Clinical Evaluation at 2, 3, 4, and 5 Years ( $\pm 30$ Days) Postoperatively**

**7.2.7.1** Telephone follow-up.

**7.2.7.2** Record adverse events.

## **7.2.8 Trial Study Flowchart**

|                   |                                 |                                  |
|-------------------|---------------------------------|----------------------------------|
| Experimental flow | Screening period (Preoperative) | Follow-up period (postoperative) |
|-------------------|---------------------------------|----------------------------------|

| Visit Number                                                  |                           | V1     | V2                             | V3                         | V4         | V5      | V6           | V7        | V8      | V9         | V10        |
|---------------------------------------------------------------|---------------------------|--------|--------------------------------|----------------------------|------------|---------|--------------|-----------|---------|------------|------------|
| Days                                                          |                           | -30d~0 | Device
implant
a
tion | Discharg
e or
30d±7d | 3M±15
d | 6 M±30d | P12M±30
d | 2Y±3
d | 3Y ±30d | 4Y±3
0d | 5Y±3
0d |
| Informed Consent                                              |                           | X      |                                |                            |            |         |              |           |         |            |            |
| Inclusion/Exclusion
Criteria                               |                           | X      |                                |                            |            |         |              |           |         |            |            |
| Medical
history                                            |                           | X      |                                |                            |            |         |              |           |         |            |            |
| Vital Signs (BP, P)                                           |                           | X      | X                              | X                          |            |         |              |           |         |            |            |
| NYHA Functional
Class                                      |                           | X      |                                | X                          | X          | X       | X            |           |         |            |            |
| ECG                                                           |                           | X      |                                | X                          | X          | X       | X            |           |         |            |            |
| Laboratory
Tests
1, 3                                   | Complete
Blood         | X      |                                | X                          |            |         |              |           |         |            |            |
|                                                               | Count                     |        |                                |                            |            |         |              |           |         |            |            |
|                                                               | Blood
Biochemistr
y | X      |                                |                            |            |         |              |           |         |            |            |
| Transesophageal
Doppler
echocardiograph y
(TTE) 2, 7 |                           | X 2    | X 2                            | X                          | X          | X       | X            |           |         |            |            |
| Transesophageal
Doppler
echocardiograph y
(TEE) 2, 7 |                           | X 2    |                                |                            |            |         |              |           |         |            |            |
| Blood or Urine
Pregnancy Test (if
needed) 5             |                           | X      |                                |                            |            |         |              |           |         |            |            |
| Telephone visits                                              |                           |        |                                |                            |            |         |              | X         | X       | X          | X          |
| Adverse Event
Recording                                    |                           |        | X                              | X                          | X          | X       | X            | X         | X       | X          | X          |
| Concomitant
Medications                                    |                           | X      | X                              | X                          | X          | X       | X            |           |         |            |            |
| eCRF Completion                                               |                           | X      | X                              | X                          | X          | X       | X            | X         | X       | X          | X          |

## Notes:

1. Laboratory test results and electrocardiogram (ECG) examinations conducted within 15 days prior to signing the informed consent form are valid as baseline assessments.
2. Ultrasound examination (either Transthoracic Echocardiography [TTE] or Transesophageal Echocardiography [TEE], choose one) as a baseline assessment should be performed by an ultrasound physician at our hospital before the surgery. Intraoperative Transesophageal Echocardiography (TEE) is recommended.

3. Laboratory tests include complete blood count (white blood cells, red blood cells, hemoglobin, platelets), blood biochemistry (creatinine, alanine aminotransferase, aspartate aminotransferase, total serum bilirubin), and coagulation function (activated partial thromboplastin time, prothrombin time, thrombin time).
4. Visit 3---Before discharge or 30±7 days post-operation, whichever comes first.
5. Pregnancy test: If the subject is a woman of childbearing age, a blood or urine pregnancy test should be performed as needed.
6. Record the use of antiplatelet or anticoagulant medications.
7. Cardiac ultrasound examinations should be performed by a qualified physician at our hospital; the same subject's ultrasound examinations should be conducted at the same center; follow-up results will be independently interpreted by a senior ultrasound physician.
8. The surgery should be performed by a designated surgeon.

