## Protocol Synopsis

|                            |                                                                                                                                                                                                                                              |
|----------------------------|----------------------------------------------------------------------------------------------------------------------------------------------------------------------------------------------------------------------------------------------|
| Name of the trial   | A prospective, multicenter, randomized, controlled clinical trial evaluating the safety and efficacy of heart valve prosthetic rings for the treatment of tricuspid regurgitation                                                            |
| Test equipment      | Annuloplasty Ring                                                                                                                                                                                                                            |
| Experiment al stage | Clinical validation of Class III medical devices                                                                                                                                                                                             |
| Research design     | Prospective, multicenter, randomized controlled, non-inferior                                                                                                                                                                                |
| Test equipment      | Investigational Device: Annuloplasty Ring (Beijing Permed Biomedical Engineering Co.,Ltd)
Control Device: Edwards MC3 Ring (Edwards Lifesciences (Shanghai) Medical Products Co., Ltd.)                                                   |
| Sample capacity     | 164 cases                                                                                                                                                                                                                                    |
| Study population    | Patients with tricuspid valve insufficiency.                                                                                                                                                                                                 |

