| 
Statistical Methods:
 
This trial plans to enroll 164 patients, who will be randomly assigned to either the experimental group or the control group in a 1:1 ratio, with 82 cases in each group.
 
The primary endpoint of this clinical trial is the success rate of valve repair at 6 months postoperatively, defined as no severe regurgitation and an increase in annular diameter of <math>\leq 15\%</math> based on echocardiographic evaluation. According to literature reports and clinical experience, the expected success rate of valve repair in the control group at 6 months postoperatively is 95%. Assuming that the investigational medical device can achieve comparable efficacy, the clinically accepted non-inferiority margin is set at -10%. With a one-sided significance level of 0.025 and a power of 80%, the sample size was estimated using PASS 14.0 software, indicating that 75 cases are required for each group. Considering potential dropouts during the study, the plan is to enroll 82 cases per group, totaling 164 cases.
 
The trial results will be determined based on the difference in the primary efficacy endpoint between the experimental group and the control group. If the lower limit of the 95% confidence interval for the difference in success rates between the experimental group and the control group is
 |                                                                                                                                                                                                                                                                                                                                                                                                                                                                                                                                                                                                                                                                                                                                                                                                                                                              |

greater than -10% (the predefined non-inferiority margin), the non-inferiority conclusion will be established. Otherwise, the non-inferiority conclusion will not be supported.

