## 5.2 Structural Composition, Working Principle, and Mechanism of Action

The Annuloplasty Ring comprises the following layers:

**Base layer:** A closed-loop nitinol tube connected with nitinol wires. **Intermediate layer:** A silicone layer with a suture border, filled with long-term implantable silicone between the base and intermediate layers. **Outer layer:** A biocompatible polyester fabric. The Annuloplasty Ring is designed for tricuspid valve repair. Its three-dimensional oval shape matches the natural tricuspid valve orifice. The ring comes pre-attached to a sterile, single-use holder for simplified implantation. The holder and sizing device are packaged separately as non-sterile components, requiring cleaning and steam sterilization before reuse.

prosthetic ring

[figure not shown]

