### **7.1.3 Measures to Reduce and Avoid Bias**

To ensure the reliability and validity of the trial results, bias will be minimized through the following three key strategies:

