### **7.1.6 Efficacy Evaluation Methods**

#### **7.1.6.1 Description of Efficacy Parameters**

Primary efficacy endpoint: The success rate of valve annuloplasty repair at 6 months postoperatively, defined as no severe regurgitation and an increase in diameter  $\leq 15\%$  (based on a comprehensive assessment of regurgitation severity and diameter increase).

Other efficacy endpoints:

**7.1.6.1.1** At discharge or 30 days postoperatively (whichever comes first), 3 months, 6 months, and 12 months:

- Degree of valve regurgitation assessed by echocardiography (evaluated according to the tricuspid regurgitation assessment index table).
- Changes in echocardiographic parameters (right atrial and ventricular size, diameter, width of the narrowest regurgitation jet, and reverse flow area).
- NYHA functional class.
- Freedom from reoperation due to tricuspid valve insufficiency.

**7.1.6.1.2** Evaluation of the trial device's performance, including needle insertion smoothness and user-friendliness of the ring holder.

**7.1.6.1.3** Technical success rate of the surgery (before leaving the operating room), defined as no intraoperative death, successful implantation of the annuloplasty ring, successful removal of the ring holder, and no emergency surgery or secondary

intervention related to the trial device.

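### The protocol specifies no masking to device for the physician who interprets the follow-up echoes, although the primary endpoint is read entirely from echo

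*Protocol*

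**What the plan says.** **Who scans and who reads.** Note 7 to the flowchart in Protocol 7.2.8 separates two tasks. For the scan: "Cardiac ultrasound examinations should be performed by a qualified physician at our hospital". For the reading: "follow-up results will be independently interpreted by a senior ultrasound physician". The note gives no location, affiliation or masking status for the interpreting physician.

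**Bias controls.** Section 7.1.3 states that "bias will be minimized through the following three key strategies". The three are randomisation, investigator training and clinical monitoring.

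**Design label.** The Synopsis describes the trial as "Prospective, multicenter, randomized controlled, non-inferior". It says neither open-label nor masked.

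**Endpoint.** Success at 6 months means no severe regurgitation and a diameter increase of at most 15%. Section 7.1.6.1 says this is "based on a comprehensive assessment of regurgitation severity and diameter increase", and the statistical part of the Synopsis says "based on echocardiographic evaluation". Section 7.1.6.2 grades regurgitation as severe from a jet area of 10 cm² or an area fraction of 33%. It takes annular diameters as the mean of three diastolic measurements.

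**Device identity.** Section 7.2.2 reads: "Perform surgery using the designated device according to randomization results, recording anesthesia method, device model, and device performance evaluation". Nothing in the protocol withholds that record from later readers.

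**The concern.** Both components of the primary endpoint are read from images by a person. Randomisation balances the patients but not the readings. Training standardises procedure. Monitoring compares the case report form with the source, so it detects transcription errors, not a grade influenced by knowing the ring.

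A site could follow the protocol to the letter and still hand the reader the operative report with the device model on it. Such knowledge could shift borderline grades towards either arm, or pull the arms together, which in a non-inferiority trial favours the claim. About 5% of patients are expected to fail in the control arm, so the verdict rests on a handful of readings.

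This is not a detail for the statistical analysis plan. What the reader knows has to be fixed before follow-up images are interpreted, because an analysis plan cannot mask readings already made.

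**Working it through.** **1. Is any masking specified?** Side by side:

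| Place in Protocol | Content | Masking stated? |
|---|---|---|
| Synopsis, 7.1.2 | Prospective, multicentre, randomised, controlled | No |
| 7.1.3 | Randomisation, training, monitoring | No |
| 7.2.2 | Device model recorded at surgery | No concealment from later readers |
| 7.2.8, Note 7 | Hospital physician scans; senior physician interprets independently | No |
| 7.1.7.2 | Independent event committee for device-related serious adverse events | Does not rule on the echo endpoint |

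No section masks the patient, the sonographer or the reader.

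**2. The plan's own sample size.** Inputs from 8.2.1: success 95% in both arms, margin 10 points, one-sided alpha 0.025, power 80%.

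n = (1.960 + 0.842)² × (0.95×0.05 + 0.95×0.05) / 0.10² = 74.6, rounded up to **75 per arm**, as stated. Masking does not enter this formula, so the fix leaves 75 evaluable and 82 enrolled per arm unchanged.

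**3. What differential reading could do to the error rate.** The decision rule (8.1.5 and Synopsis) is that the lower limit of the Newcombe two-sided 95% interval exceeds -10%:

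lower limit = (p₁ − p₂) − √[(p₁ − l₁)² + (u₂ − p₂)²], where l₁ is the Wilson lower limit in the test arm and u₂ the Wilson upper limit in the control arm.

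The probability of passing was obtained by summing binomial probabilities over all pairs of outcomes. The control rate is 95% and the true test rate is 85%, exactly at the margin. If a share f of true test failures is read as success, the observed test rate is 0.85 + 0.15f.

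| f (assumed) | Observed test rate | Non-inferiority declared, 75 per arm | 82 per arm |
|---|---|---|---|
| 0 | 85.0% | 2.6% | 2.4% |
| 10% | 86.5% | 5.0% | 4.7% |
| 20% | 88.0% | 9.3% | 9.0% |
| 30% | 89.5% | 16.4% | 16.2% |

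**4. The opposite direction.** With both true rates at 95% and 75 per arm, the same enumeration gives a 71.8% chance of passing. If the test arm is read 2 points worse (93% against 95%), the chance falls to 47.4%. Unmasked reading therefore exposes the sponsor as well.

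**5. Sensitivity at the edge.** With 82 per arm and 78 control successes (95.12%, Wilson upper limit 98.09%):

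- 76 test successes (92.68%, Wilson lower limit 84.94%): −2.44% − √(7.74² + 2.97²)% = **-10.73%**, fail.
- 77 test successes (93.90%, Wilson lower limit 86.51%): −1.22% − √(7.39² + 2.97²)% = **-9.19%**, pass.

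One patient reclassified changes the verdict here. The same happens at 75 per arm against 71 control successes: 69 gives -11.65% and 70 gives -9.97%.

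**The case against.** **The protocol is silent, not contrary.** A reader might infer that the decisive readings are unmasked. The text does not say so. It says that interpretation is independent and leaves masking open. This stands: the point is an unspecified safeguard, not a stated defect.

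**The reader need not be a site physician.** A reader might also infer that someone at the treating hospital grades the endpoint. In Note 7 the hospital applies to the person who performs the scan, and the interpreter has no stated location. This also stands.

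**The list in 7.1.3 is not exhaustive.** The independent reading in Note 7 is itself a bias control and is not among the three. Absence from 7.1.3 alone therefore proves little. The evidence is that no section specifies masking.

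**Discretion is limited.** Section 7.1.6.2 gives numeric cuts for severe regurgitation, averages three diameters, and treats an increase as significant only when both diameters exceed 15%. The comprehensive assessment may mean no more than combining two components. This narrows the concern without closing it. The jet is measured in the view showing most regurgitation, and choosing that view, tracing the jet and placing the calipers remain with the reader.

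**The one-patient flip does not measure bias.** Any single event, whatever its cause, flips a result placed at the edge. The example also assumes that the reclassified patient meets the other criterion and, at 82 per arm, that nobody drops out. It shows how sensitive the rule is, not how large a masking effect would be.

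**Conclusion.** The point holds as a gap in the design. The protocol specifies no masking to device for the physician whose independent interpretation covers the follow-up echoes, and the primary endpoint comes wholly from those echoes. The documents do not show that readings will be unmasked, that they will be biased, or in which direction.

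The size of any bias is unknown. The rise from 2.6% to 5.0%, 9.3% or 16.4% is an illustration. It rests on three assumptions: a true test rate exactly at the margin, 75 evaluable patients per arm, and misreading of 10%, 20% or 30% of failures in the test arm only. The protocol gives no figure for reading error. The illustration does show that a shift of 1.5 points (0.10 × 15%) is enough to roughly double the false-positive rate.

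This should be changed, because the remedy is cheap and has to be in place before the readings are made.

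**What to change.** In Note 7 and in 7.1.3, state that:

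- the independent reader already planned interprets de-identified follow-up images without access to the allocated arm, the device model or the operative report, and without the centre where reading is off-site;
- this reader's regurgitation grade and diameters determine the primary endpoint;
- masking may be incomplete. Section 5.2 describes the test ring as "A closed-loop nitinol tube connected with nitinol wires", while section 4.2 describes the MC3 control ring as C-shaped, so the two may be distinguishable on some images. That is an inference from their shapes.

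**Cost.** The work of de-identifying images, and masking that will be imperfect. Withholding arm, device model and operative report needs no extra scan or reader and leaves sample size and alpha as they are. Withholding the centre as well would need off-site reading, which the protocol does not describe; it is therefore conditional here.
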